### Sample size and sampling strategy

#### Household survey

Baseline data from the Bangladesh Health and Demographic Survey 2017–18 indicate a 40% care-seeking rate among children under five with suspected pneumonia in the four weeks preceding the survey [39]. Assuming a baseline value of care-seeking practice for childhood illness among children under five years of age with suspected pneumonia in the past four weeks is 40% in baseline and (based on our objectives) 80% in end-line, and setting a 5% margin of error and 95% confidence interval, the unadjusted sample size is 23 children under five years of age with suspected pneumonia per district, increasing to 58 after adjustment for a 20% non-response rate and a design effect of 2.0. To achieve this sample size, we will need to reach 5121 households and 20 480 population per district. For the household survey, we will use a stratified sampling technique to ensure equal representation. Specifically, we will select villages, considered as the primary sampling unit, through probability proportional to size sampling, after which we will identify and interview all women with under-five children in the sampled villages.

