## METHODS

The goal of this study is to achieve high and effective population coverage of pneumonia treatment in under-five children in Bangladesh and to develop a scalable implementation strategy for contextual adaptation to other low- and middle-income countries (LMICs).

Our primary objective is to increase access to pneumonia treatment in under-five children to achieve high (≥80%) and effective population-based coverage (*i.e.*, patients receiving the full course of pneumonia treatment) in the study area. We also set five secondary objectives:

to increase care-seeking practices from appropriate healthcare providers for general danger signs and pneumonia-related signs of under-five children;to determine the rate of clinical treatment failure of young infants 7–59 days old with fast breathing and children 2–59 months old with fast breathing and/or chest indrawing pneumonia who received treatment from CHCPs;to assess the compliance with pneumonia treatment among young infants 7–59 days old with fast breathing and children 2–59 months old with fast breathing and/or chest indrawing pneumonia who received treatment from CHCPs;to explore the knowledge, perceptions, and experiences of health facility staff, CHCPs, and beneficiaries on the implementation of pneumonia management;to improve the availability of essential commodities in the CCs to manage pneumonia in under-five children.

We will achieve these objectives through three activities: designing an implementation delivery package for introducing the EMPIC in Bangladesh (activity 1); employing a continuous learning process during the implementation period to understand the prerequisites for the scale-up of the package (activity 2); and assessing whether the implementation delivery package worked by documenting the implementation process, understanding and assessing care practices, and exploring the experiences of health managers, health service providers, and caregivers related to the implementation of the package (activity 3).

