### Study outcome

The primary outcome of interest is high (≥80%) and effective (patients receiving the full course of pneumonia treatment) coverage among under-five children (**Table 3**). The secondary outcome of interests are: treatment failure rate among young infants 7–59 days old with fast breathing and children 2–59 months old with chest indrawing and/or fast breathing pneumonia who received treatment from CCs; availability of essential commodities and supplies for managing childhood pneumonia; CHCPs’ knowledge of managing childhood pneumonia; caregiver’s knowledge and care-seeking practices regarding childhood pneumonia; and prevalence of pneumonia among under-five children, utilisation of CCs for pneumonia related symptoms; and treatment compliance.

**Table 3 T3:** Study enrolment and outcome assessment strategy

Activity	What	Who	When	Where	How
Case identification	Identify young infants with fast breathing pneumonia and children aged 2–59 months with fast breathing and/or chest indrawing pneumonia from data extracted from the service registers	Trained data extractors appointed by the study team	Twice in a week	Health facilities (CCs and union-level health facilities)	Trained data collectors will extract data from the registers or case record forms in the health facilities. From there, they will identify young infants with fast breathing pneumonia and children aged 2–59 months with fast breathing and/or chest indrawing pneumonia. They will provide this information to study-appointed nurses/paramedics who will conduct enrolment of the participants.
Screening and Enrolment	Enrol eligible young infants and children aged 2–59 months based on inclusion and exclusion criteria	Study appointed nurses or paramedics	One to three days after facility visit	Phone	Nurses and paramedics will screen the children based on the inclusion and exclusion criteria from the information received from study-appointed data extractors. They will contact the caregivers of the eligible children over the phone and take verbal consent for the home visit. They will enrol the children if consent is given by the caregivers.

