### Data analysis

We will use descriptive statistics to report the readiness of CCs for pneumonia case management, knowledge of CHCPs, utilisation of CCs by under-five children, and treatment compliance by caregivers, treatment failure rates, knowledge of caregivers regarding general danger signs and pneumonia danger signs, and care-seeking by caregivers for under-five children. Changes in these indicators will be presented quarterly. We will score health facility readiness based on the availability of essential items for managing pneumonia cases according to national guidelines and consultations with the clinical experts and national health managers. We will categorise facility readiness based on item availability as poor (0–50%), moderate (50–75%), and good (75–100%).

We will calculate treatment compliance based on caregiver recall of giving prescribed antibiotics from CCs at home, collected through the follow-up interviews with caregivers. Data will be analysed using Stata, version 16.0 (StataCorp LLC, College Station, Texas, USA).

We will base our qualitative analysis on a thematic approach. First, multiple researchers will code a minimal set of transcripts to establish intercoder reliability, after which a master code-list will be created for the remaining transcripts. We will compare the new and earlier data iteratively data to identify similarities and differences.

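### The household-survey size of 23 (58 after inflation) per district does not follow from the stated 5% margin of error; the survey estimates care-seeking to about ±16 points at 80%

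*Protocol article*

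**What the plan says.** Under Household survey, the protocol article takes it that care-seeking in "children under five years of age with suspected pneumonia in the past four weeks is 40% in baseline". The endline assumption is given as "based on our objectives) 80% in end-line". The article then derives the size by "setting a 5% margin of error and 95% confidence interval, the unadjusted sample size is 23 children under five years of age". That figure applies to each district, and the text describes it as "increasing to 58 after adjustment for a 20% non-response rate and a design effect of 2.0". It gives no power, no sidedness and no statement that two proportions are compared.

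Two other places bear on how this is read. The primary objective in METHODS is "to achieve high (≥80%) and effective population-based coverage", and Study outcome repeats the 80% level for full-course treatment. Data analysis opens with "We will use descriptive statistics to report the readiness of CCs for pneumonia case management" and includes care-seeking in the same descriptive list, without naming a baseline-to-endline test.

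**The concern.** A margin of error of 5% at 95% confidence normally means that the estimate is known to within 5 points either way. The article uses the term in that sense in the next subsection, Community follow-up, where margins of 4% and 3% go into the single-proportion formula. Twenty-three children cannot give a 5-point margin for a proportion of 40% or 80%.

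What is at stake is how the endline survey result will be read. Care-seeking is to be reported descriptively, so the reader's trust in the percentage rests on its stated precision. If that precision is overstated three- to four-fold, a district result near 80% will look far firmer than it is, in a study meant to inform scale-up.

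**Working it through.** **Inputs, all from Household survey:** 40% at baseline, 80% at endline, 5% margin, 95% confidence (z = 1.96), 20% non-response, design effect 2.0, stated sizes 23 and 58 per district.

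**1. Can the stated basis give 23?** Single proportion, n = z² p(1−p)/d², with d = 0.05:
- p = 0.80: 3.8415 × 0.16 / 0.0025 = 245.9, so 246.
- p = 0.40: 3.8415 × 0.24 / 0.0025 = 368.8, so 369.

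These are 246/23 = 10.7 and 369/23 = 16.0 times the stated size. After the plan's own inflation they become 246 × 2.0/0.8 = 615 and 369 × 2.0/0.8 = 922.5, so 923 per district.

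**2. What does give 23?** Two proportions, pooled variance, two-sided 5%, 80% power (z = 0.8416; the power is an assumption, as the article states none):
- mean proportion = 0.60
- n = [1.96 × √(2 × 0.60 × 0.40) + 0.8416 × √(0.40 × 0.60 + 0.80 × 0.20)]² / 0.40²
- = (1.358 + 0.532)² / 0.16 = 22.3, so 23 per survey round.

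This match is not unique. A one-sided 5% comparison with continuity correction at 80% power also rounds up to 23 (22.2). Other variants do not match: unpooled variance gives 20, arcsine 22, two-sided with continuity correction 28, and two-sided 90% power without correction 30.

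**3. Is the inflation right?** 23 × 2.0 / (1 − 0.20) = 57.5, so 58. Yes.

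**4. How is margin of error used elsewhere?** In Community follow-up, 3.8415 × 0.08 × 0.92 / 0.04² = 176.7 (article: 176), and 3.8415 × 0.06 × 0.94 / 0.03² = 240.7 (article: 238). Both are close enough to show that the term there means the half-width of a confidence interval.

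**5. What precision does 58 deliver?** Responders: 58 × 0.80 = 46.4, about 46. Effective size: 46/2.0 = 23. Wald half-width, 1.96 × √(p(1−p)/n):

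| Setting | Effective n | At 80% | At 40% |
|---|---|---|---|
| One district, 20% non-response | 23 | ±16.3 points | ±20.0 points |
| One district, all 58 respond | 29 | ±14.6 points | ±17.8 points |
| Two districts pooled, 20% non-response | 46 | ±11.6 points | ±14.2 points |

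Against the stated 5 points, the per-district figures at the planned non-response are 16.3/5 = 3.3 and 20.0/5 = 4.0 times wider.

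**The case against.** The strongest reply is that the number is sound and only its label is wrong. The paragraph gives both a baseline and an endline value, so a two-proportion basis is visible; 23 reproduces on that basis, and the step to 58 is correct. This stands. It makes the fault a misstated basis and precision rather than a failed calculation or a survey too small for its apparent purpose.

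A second reply is that the two-sided test and 80% power are reconstructed, not documented. This also stands, since another standard variant gives 23 too. The authors must supply the actual inputs.

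A reader might go further and infer that the survey cannot show whether the primary target of at least 80% was met. The document does not support that, for three reasons.
- The survey is sized on care-seeking, which is a secondary objective and outcome. The primary outcome is full-course treatment coverage, and Table 2 takes its coverage indicator from routine registers. The assumed 80% is borrowed from the objectives, but nowhere are these 58 children made the test of the primary outcome.
- Even for care-seeking, it is not true at every value. With both districts pooled (effective n = 46), an exact 95% lower limit would reach 80% with probability of about 0.80 if the true value were 95%, though only about 0.31 if it were 90%.
- Requiring the lower limit to reach 80% would be a new and stricter success rule, which the article does not set.

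Nor is it informative that a district estimate has roughly an even chance of reaching 80% when the truth is exactly 80%. That holds at about any sample size, including the 246 that a true 5-point margin needs.

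**Conclusion.** The point holds as a misstated basis and precision. A 5-point margin is incompatible with 23 children per district: it needs 246 to 369 before inflation, or 615 to 923 after it. The likeliest explanation is that a 5% significance level was written as a margin of error and the power was left out; that is inference. The planned size delivers about ±16 points at 80% and ±20 at 40% per district, and about ±12 at 80% pooled.

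These figures assume the plan's 20% non-response and design effect of 2.0, 58 children per district in each round, two districts contributing equally when pooled, and the normal-approximation interval. The incompatibility with a 5-point margin depends on none of these except the normal approximation: 23 fully independent responders would still give ±16.3 points at 80%. The finding does not extend to whether the study can judge its primary coverage outcome.

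**What to change.** In Household survey:
- Remove the reference to a 5% margin of error.
- Have the authors state how 23 was actually obtained: apparently a comparison of 40% with 80% care-seeking, with its significance level, sidedness, power and whether the size is per survey round.
- State the delivered precision for care-seeking at 80%: about ±16 points per district and ±12 points pooled.
- Add that the survey is sized to detect a large rise from baseline, not to estimate a level near 80% to within 5 points.

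In Data analysis, say that endline care-seeking will be reported with a 95% confidence interval that accounts for the village sampling.

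This needs no extra households and no new success criterion. The only cost is a less favourable stated precision.

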### Study settings, period, and population

We will select two *upazilas* (sub-districts) in total: one each from the Kushtia and Dinajpur districts. From them, we will choose 20 CCs based on service availability and caseload, in consultation with national and district-level health managers. Dinajpur district covers an area of 3437.98 km^2^ and is home to 299 0128 inhabitants, resulting in a population density of 868 people per km^2^ [35]. The district has one medical college hospital, one district hospital, 12 *upazila* health complexes (sub-district hospitals), 119 union sub-centres and union health & family welfare centres (union level health centres), and 337 CCs (health outpost centres) [36]. Kushtia district has a population of 1 986 838 and covers an area of 1621.15 km^2^, leaving a density of 1073 people per km^2^ [37]. The district's health facilities include one district hospital (secondary level referral hospital), five *upazila* health complexes (sub-district hospitals), 73 union health and family welfare centres (union level health centres), and 205 CCs [36]. The study will be conducted across 24 months, where 18 months will be reserved for the delivery of the implementation package.

The study population will be under-five children presenting with pneumonia in CCs, CHCPs working in CCs, caregivers and family members of children visiting CCs, district and sub-district level health managers and supervisors and central-level health managers and policymakers.

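### Household survey: drawing villages with probability proportional to size and then interviewing every eligible woman is not self-weighting, so estimates need weights or a matched second stage

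*Protocol article*

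**What the plan says.** The Household survey section (Methods, Sample size and sampling strategy) states that "we will use a stratified sampling technique to ensure equal representation". The next sentence gives the mechanism: villages, as the primary sampling unit, are selected "through probability proportional to size sampling, after which we will identify and interview all women with under-five children in the sampled villages". Stage one is therefore a size-proportional draw of villages, and stage two takes every eligible woman in them.

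The article gives no fixed number per village, no subsampling, no measure of size and no names for the strata. The survey is sized on a care-seeking proportion that "is 40% in baseline and (based on our objectives) 80% in end-line". This yields 23 children with suspected pneumonia per district, raised to 58 for 20% non-response and a design effect of 2.0. Reaching them is expected to need 5121 households and 20 480 people per district.

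The Data analysis section begins "We will use descriptive statistics to report the readiness of CCs for pneumonia case management" and lists caregiver knowledge and care-seeking among the indicators reported in this way. Survey weights are not mentioned.

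**The concern.** Selection proportional to size gives every person the same chance of inclusion only if the second stage offsets the first, which a fixed take per village does. A take-all second stage belongs with an equal-probability draw of villages. The article combines the first stage of one scheme with the second stage of the other, so large villages are favoured at selection and then contribute in proportion to their size as well.

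The survey is meant to describe a population, and its end-line assumption is an absolute level, 80% care-seeking. If care-seeking differs between large and small villages, a simple proportion from this sample estimates a size-weighted quantity, not the proportion among children in the area.

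**Working it through.** **The plan's own figure.** A two-sided comparison of 40% with 80%, α = 0.05, pooled variance, no continuity correction, with 80% power and 1:1 allocation assumed because the article states neither:

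- n = [1.96·√(2·0.6·0.4) + 0.8416·√(0.24 + 0.16)]² / 0.4² = (1.358 + 0.532)² / 0.16 = 22.3, rounded up to 23.
- 23 × 2.0 / (1 − 0.20) = 57.5, rounded up to 58.

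Both figures reproduce and are not in dispute. They matter here only because the 58 rests on the design effect of 2.0.

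**Inclusion probability.** Let M_i be the size of village i and m the number of villages drawn. Then π_i = (m·M_i/ΣM) × 1, where the 1 is the take-all second stage. So π_i is proportional to M_i. A woman in a village of 2000 is 2000/500 = 4 times as likely to be included as one in a village of 500.

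**Share of the sample** (assumed: equal numbers of villages of 500 and 2000).

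- Population share of the large villages: 2000/2500 = 80%.
- Expected sample share: 2000²/(500² + 2000²) = 4 000 000/4 250 000 = 94%.

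**Effect on an unweighted proportion.** The target is ΣM·p/ΣM; the unweighted estimate tends to ΣM²·p/ΣM². With assumed outcomes of 60% in the small and 85% in the large villages:

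- Target: (500·0.60 + 2000·0.85)/2500 = 80.0%.
- Unweighted: (250 000·0.60 + 4 000 000·0.85)/4 250 000 = 83.5%.

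With the two outcomes exchanged, the target is (500·0.85 + 2000·0.60)/2500 = 65.0% and the unweighted value is (250 000·0.85 + 4 000 000·0.60)/4 250 000 = 61.5%. The sign follows the gradient.

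**A range of assumptions.** The articles's documents give no village sizes, so sizes were taken as lognormal with a coefficient of variation (CV) of 0.25, 0.5 or 0.75. The outcome was set to rise in equal steps across quarters of village size by 0, 10, 20 or 30 points, centred on 40%.

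| CV of village size | Largest quarter of villages: share of population | Same quarter: share of sample | Bias in points at gradient 0 / 10 / 20 / 30 | Weighting loss 1 + CV² |
|---|---|---|---|---|
| 0.25 | 33.5% | 43.0% | 0 / 0.8 / 1.6 / 2.5 | 1.06 |
| 0.5 | 41.6% | 59.9% | 0 / 1.3 / 2.7 / 4.0 | 1.25 |
| 0.75 | 50.1% | 74.8% | 0 / 1.6 / 3.2 / 4.8 | 1.56 |

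A simulation of 20 villages drawn with replacement agreed. At CV 0.5 and a 20-point gradient the target was 0.4315, the unweighted mean 0.4568 and the mean weighted by 1/M_i 0.4314.

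**Price of weighting.** With weights 1/M_i, the Kish loss is N·ΣM²/(ΣM)² = 1 + CV², where N is the number of villages. For 500 and 2000 it is 2·(500² + 2000²)/2500² = 1.36, leaving 2.0/1.36 = 1.47 of the planned design effect for clustering. At CV 1.0 the loss is 2.00 and nothing is left.

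**The case against.** The strongest reply is that the defect appears only in an unweighted analysis, and the article nowhere says the analysis will be unweighted. A weighted proportion is still a descriptive statistic, weights are commonly left to an analysis plan, and none is shown. This stands as far as it goes: a reader may infer that unweighted estimates are planned, but the text does not say so. It does not remove the point, because the two-stage rule is fixed in the article. Weighting also needs the size measure and selection probabilities kept from the draw, and it uses up part of a design effect that is already fixed.

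Further replies stand in part:

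- The wording about equal representation is attached to the stratification. It may mean equal representation of districts or of unnamed strata, so a flat contradiction cannot be claimed.
- The documents do not show the direction of any bias. The introduction lists distance to facilities among many influences on care-seeking but says nothing about village size. An upward bias is a guess.
- A bias of 3.5 points is small beside the survey's precision. With an effective 23 children per district, the half-width at 80% is 1.96·√(0.16/23), about 16 points. A stable distortion would also largely cancel in a baseline-to-end-line change, though not in the absolute level.
- If many villages are drawn without replacement, the largest enter with certainty and the imbalance shrinks. Assuming 10 clinic catchments per district of 6000 to 10 000 people each, 20 480 people would be about 20% to 34% of the frame.

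Two stronger readings are tempting. From the sizing per district, a reader might infer that villages come from whole districts or sub-districts, so that most respondents are unexposed and 80% is out of reach. The article states no such frame. It sets its objective in the study area, and the Community follow-up section uses site and district interchangeably. A reader might also infer that the primary ≥80% effective-coverage claim rests on this survey. Table 2 takes coverage from routine registers, and Activity 3 assigns the surveys to caregiver knowledge, care-seeking and treatment outcomes.

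**Conclusion.** The sampling rule as written gives inclusion probabilities proportional to village size and is not self-weighting. This follows from the two stated stages and needs no assumption beyond the size measure tracking the number of eligible women. Unless weights are applied, survey estimates such as care-seeking over-represent large villages.

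The resulting bias is zero if the outcome does not vary with village size. It is about 1 to 5 points for village-size CVs of 0.25 to 0.75 and gradients of 10 to 30 points. Those inputs are assumed, and the sign is open. The point concerns the survey's population estimates, including the 80% end-line care-seeking level. It should be settled before villages are drawn and does not invalidate the study.

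**What to change.** Choose one of three and state it in the sampling plan, together with the measure of size and the strata:

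1. **Keep the design and weight.** Record each village's size measure and selection probability at the draw. Weight respondents by the inverse of the inclusion probability, using survey methods with village as primary sampling unit. There is no extra fieldwork, but the variance rises by a factor of about 1 + CV². Compute the CV from the village list and check that 2.0 covers weighting and clustering together; if not, the 58 must rise.
2. **Keep the size-proportional draw and fix the take.** Interview a fixed number of households, or one fixed-size segment, per village. This removes the need for unequal weights but requires listing or segmenting and probably more villages. The take should be set in households, because only about 58/5121 = 1.1% as many target children as households are expected.
3. **Draw villages with equal probability and keep full enumeration.** This needs no unequal weights within a stratum, but the achieved sample size depends on which villages are drawn and is less predictable.

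Option 1 changes least. Whichever is chosen, the same rule should apply at baseline and end-line.
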